## Abstract

**Introduction:**

Opioid analgesic medications play a critical role in pain management but are associated with significant risks, including addiction. General practitioners in primary care account for a substantial proportion of opioid prescriptions, and prescribing practices may not always fully align with clinical guidelines. Given the limited evidence supporting long-term opioid use for chronic non-cancer pain, there is a pressing need for interventions that promote safer, guideline-concordant prescribing. The *Smarta Val* (Smart Choices) trial will evaluate whether a new multicomponent intervention, comprising an educational seminar, written materials and feedback on prescribing over 12 months, can improve opioid prescribing practices in primary care.

**Methods and analysis:**

This cluster randomised pragmatic trial will assess changes in opioid prescribing across primary healthcare centres (PHCCs) in Stockholm, Sweden. Consenting PHCCs will be randomised 1:1 to either the intervention group, receiving the multicomponent intervention, or the active control group, receiving a leaflet on prescribing recommendations. A sample size of 24 PHCCs per group is required to detect differences in opioid prescribing between groups. A third group of non-randomised observational reference PHCCs will be included to provide contextual information on prescribing practices during the study period. Data sources include regional healthcare databases, baseline and 12-month follow-up questionnaires, and an intervention delivery form. The primary outcome is the change in prescription of opioids at 12 months. Secondary outcomes are the change in prescription of opioids at 24 months and the change in the specific opioid substances prescribed at 12 months.

**Ethics and dissemination:**

The study has been approved by the Swedish Ethical Review Authority (Dnr 2021-06739-01). Participation in the study requires informed consent from PHCC managers in the intervention and active control groups. Results will be disseminated through international peer-reviewed journals and conference presentations.

**Trial registration number:**

NCT05577026.

STRENGTHS AND LIMITATIONS OF THIS STUDYThis cluster randomised trial evaluates a brief, scalable intervention comprising an educational seminar, written materials and feedback on opioid prescribing over 12 months.The intervention is delivered at the level of the primary healthcare centre (PHCC), targeting prescribing practices among primary healthcare professionals and reinforcing adherence to clinical guidelines.A two-year preintervention period and a 36-month postintervention follow-up allow for robust analysis of long-term prescribing trends.Inclusion of three PHCC groups (intervention, active control and observational reference) enhances internal validity and enables differentiation between intervention effects and secular trends.The trial is conducted among PHCCs in Stockholm that opted into participation, which may limit generalisability; however, the inclusion of an observational reference group supports broader contextual interpretation.

## Introduction

 Opioid analgesic medications are widely used for pain management, although caution is recommended when prescribing opioids due to the risk of adverse health outcomes, including addiction and opioid-related deaths.^1^,^3^ General practitioners (GPs) in Swedish primary healthcare account for an estimated one-third of opioid prescriptions,^4^ and although opioid prescription is declining,^5 6^ there is still room for improvement in adherence to prescription guidelines.^3 4 7^

International and Swedish clinical guidelines recommend prescribing opioids at the lowest effective dose for the shortest possible duration, as risk increases with prolonged use.^18^,^10^ Additionally, there is insufficient evidence supporting the long-term effectiveness of opioid treatment for chronic (ie, lasting for more than three months) non-cancer pain.^10^,^12^ Therefore, opioids should be reserved for selected cases within a multimodal treatment approach.^8^ Despite these clear recommendations, inconsistent application in practice persists.^7^

Prior research has identified several strategies that can effectively influence prescribing behaviour. These include social norm feedback or ‘nudging’,^13^ audit and feedback mechanisms,^14^ and feedback that is delivered frequently, by a figure of authority, and linked to clearly defined goals and action plans.^15^ Strategies to enhance prescribers’ knowledge through dissemination, education and training may improve guideline adherence.^7^ Interventions specifically targeting opioid prescribing have shown mixed results; however, those demonstrating positive outcomes often incorporate educational components (eg, academic detailing with evidence from trusted sources, workshops, continuing medical education),^16^,^19^ written materials (eg, policy documents, pamphlets),^20^,^22^ and/or audit and feedback tools (eg, memos, email reminders).^21 23 24^ These three components were therefore integrated into the intervention in the *Smarta Val* (Smart Choices) trial.

Despite promising findings in some studies, the overall quality of evidence supporting educational, policy and regulatory interventions aimed at modifying prescribing behaviour remains low.^25^ In particular, there is a lack of robust research on prescriber education targeting healthcare professionals who manage patients with chronic non-cancer pain.^26^ Given that primary care plays a central role in the initial and ongoing management of chronic pain, this represents a knowledge gap in the literature.

Furthermore, existing opioid-related interventions have been limited in both scope and context. Most originate from the US, and few have been implemented in primary healthcare settings. To date, no studies have been identified in Scandinavian countries, where differences in healthcare systems, such as regulatory frameworks, professional roles, clinical guidelines and reimbursement mechanisms, may significantly influence both implementation and effectiveness. Broader systemic and societal factors, such as healthcare access and equity, further limit the generalisability of US-based findings to the Swedish context.

To address this evidence–practice gap, we developed an intervention for Swedish primary care that integrates components with demonstrated potential to influence prescribing behaviour in real-world settings and be incorporated into routine clinical practice, aligning with the pragmatic nature of the trial. We chose to include both active control and observational reference primary healthcare centres (PHCCs) to enable comparison with standard care while also capturing real-world prescribing patterns, enhancing both internal and external validity.

### Objective

The overall objective is to evaluate, in a cluster randomised trial, the effectiveness of a new intervention that includes an educational seminar, written materials and 12 months of bimonthly prescribing feedback on opioid prescribing in primary healthcare. The intervention group will be compared with an active control group, receiving a leaflet on prescribing recommendations, and an observational reference group, continuing with usual care practices.

## Methods and analysis

### Design

This pragmatic cluster randomised trial focuses on evaluating the real-world effects of the intervention in the primary healthcare setting.^27^ Managers of invited PHCCs will consent for their centre to be randomised in the trial, which targets opioid prescribing behaviours among healthcare professionals. Prescription of opioids to registered adult patients at each PHCC, regardless of diagnosis or indication, will be followed in regional healthcare databases before and after the intervention period. The trial also includes an examination of intervention delivery, which will be reported separately. The Standard Protocol Items: Recommendations for Interventional Trials checklist^28^ was used to guide the reporting of this protocol.

### Setting

The study will be conducted among PHCCs in Stockholm County that hold a primary care contract with Region Stockholm, which is the governing body responsible for healthcare in the county.

Primary healthcare in Sweden is a comprehensive, regionally organised system comprised of public and private PHCCs within the tax-financed universal healthcare system.^29^ It is often the first point of contact for patients,^29^ and provides general medical consultations, preventive medicine and chronic disease management.^30^ In Sweden, patients are formally registered with a specific PHCC, a system that supports both continuity of care and capitation-based reimbursement.

### Eligibility and recruitment

The following steps will be used to identify eligible PHCCs:

Identify PHCCs in Stockholm County with more than 3000 registered adult patients (≥18 years) as of December 2022 (n=207).Among these, select PHCCs in the top 50% of opioid prescription volume, measured using defined daily dose (DDD) per registered patient for all opioids classified under Anatomical Therapeutic Chemical (ATC) code N02A. For these high-prescribing PHCCs (n=105), the prescribing range corresponds to 0.137–0.491 DDDs per registered patient.Send study invitations via email to managers of PHCCs meeting the above criteria.

Research coordinators will confirm eligibility with interested PHCC managers through verbal or written contact prior to obtaining written informed consent (online supplemental figure 1). Detailed eligibility criteria are presented in table 1.

**Table 1 T1:** Eligibility criteria for the *Smarta Val* trial

Category	Criteria
Inclusion	Holds a primary care contract with Region Stockholm and is thus connected to regional healthcare databases (VAL) Employs at least two full-time general practitioners
Exclusion	Has been in operation for less than 12 months

Recruitment strategies include contacting PHCC managers through up to three follow-up emails and three phone calls.

### Participant groups and interventions

The *Smarta Val* trial includes three groups of PHCCs. See table 2 for a full description of the study groups, intervention components and targeted behaviour change strategies.

**Table 2 T2:** Description of trial participant groups, intervention components and proposed behaviour change strategies

Component	Description of component	Behaviour change strategies
**Intervention group**		
90-minute educational seminar	∼60-minute PowerPoint presentation of published peer-reviewed evidence and recommendations on pain management and opioid prescription. ∼7-minute video recorded by a key opinion leader on pain treatment.	Academic detailing Inclusion of experts in the field Presentation by a figure of authority Group discussion
	∼10-minute presentation and discussion of opioid prescribing at the PHCC level and comparison of prescription levels to nearby PHCCs.	Audit of prescription trends Benchmarking to nearby PHCCs Leveraging of social norms
	∼10-minute discussion of prescribing routines at the PHCC with recommendations for how to improve practices at the clinic.	Barrier identification Intention formation (common routine) Team building Encouragement
Written materials	Physical and electronic copies of written materials, including: Example patient record templates for prescribing and deprescribing opioids. Half-page reminder summarising Wise List^36^ opioid recommendations. Longer and simplified patient–provider agreements.	Visual reminder with references Tools to be used by prescribers and for potential use with patients
Prescription feedback	Bimonthly emails over 12 months, including graphs of opioid prescription (overall DDD and substance-specific) at the PHCC.	Reminders Self-monitoring Leveraging of social norms
**Active control group**		
Leaflet on prescribing recommendations	Single-page leaflet summarising Wise List^36^ opioid recommendations and links to national^10^ and regional^35^ guidelines, emailed to PHCC managers.	Visual reminder with references
**Observational reference group**		
Usual care	Continue with usual care practices; no interventions administered.	NA

DDD, defined daily dose; NA, not applicable; PHCC, primary healthcare centre.;

### Intervention group

The intervention consists of a 90-minute educational seminar, written materials and feedback on opioid prescribing at the PHCC. While the intervention primarily targets opioid prescribers, particularly GPs, all healthcare professionals with patient contact (eg, nurses, psychologists, receptionists and medical secretaries) at the PHCC are encouraged to attend the seminar. The intervention was developed by a multidisciplinary team encompassing expertise in general medicine and pain treatment, public health, pharmacy, psychiatry, psychology, physical therapy and communication. Data sources include:

International recommendations on pain management and opioid treatment, including from Europe,^8^ the US Centers for Disease Control and Prevention,^1^ and the National Institute for Health and Care Excellence of the UK.^9^National recommendations by the Swedish National Board of Health and Welfare^12^ and Swedish Medical Products Agency.^10^Published peer-reviewed evidence by the Swedish Agency for Health Technology Assessment and Assessment of Social Services,^31^ and relevant review articles.^1132^,^34^County-specific resources, including Viss (Care Programmes and Information System in Stockholm),^35^ which provides clinical guidelines for primary care in Region Stockholm, and the Stockholm Drug and Therapeutic Committee’s Wise List,^36^ a formulary of recommended essential medicines.

Two GPs with experience in academic detailing are employed to deliver the seminar, which includes peer-reviewed evidence, a video recorded by a key opinion leader on pain treatment, general advice on tapering treatment and referral to addiction care, and presentation of prescribing patterns at the PHCC benchmarked against nearby PHCCs. Questions and discussion are encouraged throughout.

Written materials for the intervention group include provider-focused resources (patient record templates and a summary of the Wise List^36^ opioid prescribing recommendations), and patient–provider agreements for prescribers, which may also be used with patients. Physical copies will be distributed during the seminar, and all written materials and the presentation will be shared electronically afterwards. Bimonthly feedback on opioid prescribing, including overall and substance-specific DDDs, will be emailed to seminar attendees and PHCC managers for 12 months (online supplemental figure 2). The mailing list will be updated on request by the PHCC manager.

Consistent with the pragmatic trial design, participating healthcare professionals will determine the manner and frequency of study material use. During the seminar, PHCC managers will be asked to complete a baseline questionnaire. 12 months after the seminar, managers will be notified that the intervention period has ended and invited to complete a follow-up questionnaire.

### Active control group

Managers of PHCCs in the active control group will receive a single-page leaflet summarising the Wise List^36^ opioid prescribing recommendations and links to national and regional guidelines (Swedish Medical Products Agency^10^ and Viss^35^). The leaflet will be emailed once, without instructions for use. Managers will be contacted again after 12 months and will be asked to complete a follow-up questionnaire.

### Observational reference group

PHCCs in the observational reference group are not randomised, receive no study intervention and continue with usual care practices.

### Outcomes

#### Primary outcome

Change in prescription of opioids at 12 months, measured by average DDD of opioids per patient month.

#### Secondary outcomes

Change in prescription of opioids at 24 months, measured by average DDD of opioids per patient month.Change in the opioid substances prescribed at 12 months, measured by average DDD of opioids per patient month, based on ATC classification codes.

#### Other outcome measures

Change in number of patients with opioid prescriptions at 12 months, measured as the number of patients with either new or continued opioid prescriptions.Change in number of patients with an initial (new) opioid prescription at 12 months, measured as the number of opioid-naïve patients initiating opioid therapy.

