### Randomisation and blinding

#### Allocation to the intervention or the active control group

Consenting PHCCs will be enrolled on a rolling basis and randomised in a 1:1 parallel design to either the intervention or active control group. Randomisation will be pairwise, stratified by PHCC size, using computer-generated random numbers. PHCCs unmatched due to uneven numbers at a given time point will be carried forward to the next randomisation date, and any remaining unmatched PHCCs will be randomly allocated to either group.

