#### Regional healthcare databases

VAL is the name of the centralised data warehouse for monitoring healthcare utilisation in Region Stockholm.^37^ The regional healthcare databases in VAL include comprehensive healthcare records on all residents, including the PHCCs at which patients are registered, inpatient and outpatient visits, and prescriptions.

Data on the study population will be extracted from the databases for the five-year study period. At the level of the PHCC, variables include ownership type (public or private sector) and sociodemographic classification. Patient-level variables include data on PHCC registration, sociodemographic characteristics (eg, age, sex, Mosaic socioeconomic classification), and healthcare utilisation (eg, prescriptions, diagnoses and visit types).

Opioid prescribing will be quantified using dispensed DDDs, a WHO standard measure based on the assumed average maintenance dose for a drug’s main indication in adults,^38^ which is available in VAL. Key data to assess study outcomes include PHCC registration, prescribing PHCC, opioid ATC code, dispensation date, DDD per package, and the number of packages dispensed. Variables that will be used in the analysis of primary and secondary outcomes are listed in table 3. Additional variables such as migration events and date of death may also be included.

**Table 3 T3:** Variables and descriptions from the regional healthcare databases (VAL) used to assess primary and secondary outcomes

Variable	Description
Registered patients per PHCC	Calculated from the number of individual registered patients at a PHCC each calendar month
Size of PHCC	Classification of PHCC size calculated from the number of registered patients: small (<5500), medium (5500–8500) or large (>8500)
PHCC registration	PHCC name, where a patient is registered each calendar month
ATC code	Seven-digit ATC code identifying the opioid substance prescribed
Prescribing PHCC	Name of the prescribing PHCC
Dispensation date	Date opioid was dispensed
Package DDD	DDDs per package dispensed
Number of packages	Number of packages dispensed

ATC, Anatomical Therapeutic Chemical; DDD, defined daily dose; PHCC, primary healthcare centre.

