#### Analyses of primary and secondary outcomes

Analyses of primary and secondary outcomes will be conducted at the PHCC level, with comparisons made between the intervention group and the active control group, as well as between the intervention group and the observational reference group. Patients registered at the PHCCs at any point during the 12 months before and 12 or 24 months after the intervention will be included in the analyses.

The number of dispensed DDDs of opioids and the number of patient-months (ie, the number of months during which patients are registered at a given PHCC) will be summarised for each PHCC. The change in DDDs per patient-month from baseline to follow-up will be calculated for each PHCC.

The difference in change between the groups will be estimated using linear regression, with baseline prescribing (DDDs per patient-month) and the matching variables accounted for in the analysis. Cluster effects at the patient level will not be adjusted for, as the unit of analysis is the PHCC. The assumption of normality will be assessed by inspecting the model residuals. Estimated effect sizes will be reported with p values (two-sided, α=0.05) and 95% CIs. A sensitivity analysis using morphine milligram equivalents may be used as a complement to DDDs to account for potency differences between opioid substances. Exploratory subgroup analyses based on characteristics of patients at participating PHCCs may also be conducted.

Cluster-level analyses will be based on register data from regional healthcare databases, which have full coverage of prescription data; missing data are not anticipated.

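### The two other outcomes are changes in raw patient counts per PHCC, so they mix list change and list size with prescribing; both should be rates.

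*Protocol article*

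**What the plan says.** The protocol article lists two outcomes under Other outcome measures, both as changes at 12 months. The first is "measured as the number of patients with either new or continued opioid prescriptions". The second is "measured as the number of opioid-naïve patients initiating opioid therapy". Neither has a denominator.

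The other outcomes are on a different scale. The primary outcome reads "Change in prescription of opioids at 12 months, measured by average DDD of opioids per patient month", and both secondary outcomes use the same unit. The section on analyses of primary and secondary outcomes carries this through: "The change in DDDs per patient-month from baseline to follow-up will be calculated for each PHCC". That section covers only primary and secondary outcomes and applies patient-months only to DDDs.

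Three other statements bear on the point:

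- **Open lists.** For the primary and secondary analyses, "Patients registered at the PHCCs at any point during the 12 months before and 12 or 24 months after the intervention will be included"; people therefore enter and leave during the windows.
- **List size.** Eligibility requires more than 3000 registered adults. Table 3 classes PHCCs by registered patients as "small (<5500), medium (5500–8500) or large (>8500", with no upper limit.
- **Denominator available.** Table 3 already lists registered patients per PHCC: "Calculated from the number of individual registered patients at a PHCC each calendar month".

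The randomised groups are formed as follows: "Randomisation will be pairwise, stratified by PHCC size, using computer-generated random numbers". The observational reference group is not randomised.

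**The concern.** These two outcomes are the only listed ones that can show whether a change in DDDs comes from fewer users and starters or from less opioid per user. A raw count serves this purpose poorly. It rises and falls with the list when prescribing is unchanged, and the same relative effect counts for more at a large PHCC than at a small one. Nor can it be set beside a DDD rate, because one has been divided by the registered population and the other has not.

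At stake are the precision of the randomised comparison on these two outcomes, and the soundness of any before-after reading or comparison with the reference group.

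**Working it through.** **1. The plan's own sample size, as a yardstick.** The article gives 24 PHCCs per group for a 10% difference on opioid prescribing, with 80% power, 5% two-sided and covariate correlation r = 0.39. It gives no SD, so the figure can only be solved backwards:

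- residual SD = 0.10 / [(1.960 + 0.842) × √(2/24)] = 12.4% of the mean
- change-score SD = 12.4% / √(1 − 0.39²) = 13.4% of the mean

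This is plausible but cannot be checked. The point below does not depend on it; the 10% serves only as a reference effect.

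**2. Arithmetic that needs no assumed prevalence.** Count = list size × proportion with an opioid prescription.

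- Proportion constant, list up 5%: count × 1.05, a 5% rise with no change in prescribing.
- A true 10% fall is hidden when 0.90 × (1 + g) = 1, so g = 1/0.90 − 1 = 11.1%.
- The same relative effect at two list sizes: 8500 / 3001 = 2.8 times the count change.

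**3. In patients, assuming 8% have an opioid prescription** (the article gives no prevalence):

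| List at baseline | Count at baseline | List +5%, no effect | List +10%, no effect | True 10% fall, stable list |
|---|---|---|---|---|
| 3001 | 240 | +12 | +24 | −24 |
| 8500 | 680 | +34 | +68 | −68 |

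Divided by registered patients, the change in the two no-effect columns is zero.

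**4. What this does in the randomised comparison.** Simulation of 24 v 24 PHCCs, eight per size class in each group, 2000 runs per cell. All of the following are assumptions:

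- list sizes uniform within 3001–5500, 5500–8500 and 8500–14000
- mean prevalence 8% (SD 1.5 points)
- SD 5% in each PHCC's true relative change
- Poisson counts
- linear regression of change on group, baseline value and size class

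Percentage of runs with p < 0.05, counts / rates per 1000 registered:

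| SD of list change between PHCCs | No effect, equal mean growth | No effect, one group grows 5 points more | True 10% fall, equal mean growth |
|---|---|---|---|
| 3% | 4.8 / 4.8 | 48.3 / 4.9 | 97.7 / 98.9 |
| 5% | 5.5 / 4.8 | 40.8 / 5.4 | 95.2 / 98.9 |
| 10% | 5.1 / 5.1 | 22.0 / 5.0 | 73.7 / 98.8 |

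Monte Carlo error at 5% is √(0.05 × 0.95 / 2000), about 0.5 points, so the first results column is nominal for both scales. The last column shows the loss of power: about 1, 4 and 25 points. The middle column shows what a systematic difference in growth does to counts: a false difference of about 29 to 30 patients per PHCC, with rates unaffected. The assumed noise puts the rate analysis near the ceiling, so these powers are not the trial's own; only the contrast between the two scales is informative.

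**5. How likely is a 5-point growth difference by chance under randomisation?** The standard error of the difference in mean growth is SD × √(2/24): 0.87, 1.44 and 2.89 points for SDs of 3%, 5% and 10%. Five points is then 5.8, 3.5 and 1.7 standard errors. The middle column therefore does not describe what randomisation would usually produce. It describes groups whose growth differs for a systematic reason.

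**The case against.** The strongest reply is that the article does not say how these outcomes will be modelled. Its regression is specified for primary and secondary outcomes only, and an unseen analysis plan could add an offset or list-size adjustment to a count. That is correct as to the model. But the outcome itself is stated here, as a change in a number of patients, and nothing in the article supplies a denominator for it.

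A reader might infer more: that list growth can make unchanged prescribing look like an effect in the main comparison, or that chance imbalance in growth across about 24 PHCCs per group biases it. The documents do not support this. Allocation is 1:1, pairwise and stratified by size, so starting list size is balanced by size class and growth common to both groups cancels in expectation. Chance differences in growth are random error, already reflected in the standard error; with equal mean growth the rejection rate on counts stays near 5%. The article also gives no mechanism by which the intervention would change list growth.

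It is fair, too, that the loss of power is slight if list change varies little, that the 10% target was set for opioid prescribing and not for these counts, and that the two outcomes rank below secondary. What stands is that stratification and baseline adjustment deal with starting size, not with list change after baseline, and that neither randomisation nor stratification protects a before-after reading or a comparison with the reference group.

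**Conclusion.** The point holds as a weakness in the definition of two lower-ranked outcomes. As written, both mix list change and list size with prescribing. The proportional results (5% for 5%, 11.1% hiding 10%, 2.8-fold between 3001 and 8500 patients) follow from arithmetic alone.

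For intervention versus active control, the consequence is lost precision with a nominal type I error. Under the stated assumptions the loss is 1 to 4 points of power at a list-change SD of 3% to 5%, and about 25 points at 10%. The article gives no figure for this spread, so no single loss, and no sample-size multiplier, can be attributed to the trial.

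For within-group changes, and for any comparison of these outcomes with the non-randomised reference group, differing list growth can bias the result. The article plans that comparison for the primary and secondary outcomes and does not say whether it extends to these two. No primary or secondary conclusion is affected.

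**What to change.** Define both outcomes as rates over the same windows as the primary outcome:

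- patients with at least one opioid dispensing, per 1000 registered patients or per patient-month;
- new starters on the same basis, preferably with registered opioid-naïve patients as the denominator.

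Analyse them with the baseline-adjusted PHCC-level linear model used for the primary outcome, or with a count model that has log patient-months as offset. Raw counts can still be reported descriptively.

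No new data collection is needed: monthly registered patients, PHCC registration and dispensation dates are already in Table 3. The opioid-naïve denominator takes some extra derivation from the dispensing histories. The one real cost is a dated, justified amendment, since seminar visits ran from June 2023 to February 2024 and follow-up is under way or complete. It is best made before these outcomes are analysed by group. If the unseen analysis plan already has a denominator or offset, aligning the published definition with it is enough.
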